#### Follow-up

Upon completion of the 4-week treatment period, there is a further 6-month follow-up period. The research staff will continue to follow the participants via telephone communication and short messaging service (SMS). The frequency of follow-up is monthly and we will keep a record of the assessment of symptoms and medication compliance or changes. In the event of participants discontinuing or deviating from intervention protocols, the study staff will record the reasons for this and their medications and then exclude the participants from the study, and the latest outcome data including symptoms and frequency of the attacks.

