#### Primary outcome measure

The average change in the TNSS will be measured blindly by comparing the baseline score in each group with that at 6 months after treatment during the follow-up period. The TNSS is determined in terms of the severity of rhinorrhea, nasal itching, nasal obstruction, and sneezing.

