### Statistical analysis

#### Sample size calculation

The sample size calculation was performed with SAS 9.3 software (SAS Institute Inc., Cary, NC, USA) in the Clinical Evaluation Center of CACMS. The mean change in TNSS before and after treatment was used as the indicator for the efficacy evaluation in the calculation of the sample size. Results from our previous studies showed that the mean TNSS change was 4.90 ± 3.54 after acupuncture treatment [27] and 3.4 ± 1.0 after loratadine treatment [28]. Thus, we performed a non-inferiority test to calculate the appropriate trial sample size with 80 % power, alpha of 0.05, and an acceptable delta of 0.2. The results showed that a clinically important difference can be detected by a sample size of at least 39 in each group. This number was then increased to 49 per group (total of 98) to allow for a predicted 20-% dropout rate.

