#### Statistical methods

The statistical analysis will be performed with SPSS 17.0 software (SPSS Inc., Chicago, IL, USA) in the Clinical Evaluation Center of CACMS. We will perform baseline adjusted analyses for the following variables (the center and severity), and the baseline value of the corresponding outcomes will be assessed. The data analyses will be conducted on an intention-to-treat population. Descriptive statistics will be used to compare the baseline measures and patients’ characteristics between the two groups. Regarding the primary and secondary outcome measures, the two-sample *t* test or Wilcoxon rank sum test will be used to compare the differences between the two groups from baseline to the end of treatment (*p* < .05 will be considered statistically significant). If an imbalance occurs in baseline characteristics between the two groups, ANCOVA will be applied.

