#### Missing data and sensitivity analysis

The data used in the main statistical analysis should be collected in the fourth week of the treatment and at the half-year follow-up. In order to avoid missing data, we will provide an economic compensation for participants who have finished the trial and provided the completed data. The investigators have a wealth of experience in managing patients and collecting data in previous trials. They record the contact information of participants and keep in touch with them through a variety of means during the treatment and follow-up periods.

If the data are not obtained, we will record the time and reason for the missing data and will analyze the assumed missing data mechanism. For these missing data, we will use the multiple imputation adjustment approach. After the main analysis, we will perform a sensitivity analysis for the various datasets to enable us to judge the impact of missing data on our results.

A fully specified statistical analysis plan will be written independently.

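### Participants who discontinue or deviate are excluded from the study, so the month-6 TNSS that the intention-to-treat analysis needs is not collected for them

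*Protocol article*

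**What the plan says.** The Follow-up section sets the rule. Its trigger is broad: "In the event of participants discontinuing or deviating from intervention protocols", with no threshold of severity. The action is that "the study staff will record the reasons for this and their medications and then exclude the participants from the study". The sentence then trails off with "the latest outcome data including symptoms and frequency of the attacks". The grammar leaves open whether these data are recorded or discarded. Either way they are the last data before exclusion.

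The related parts of the protocol are:

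- **Discontinuation of the intervention:** severe adverse events, the participant's own wish and non-permitted drugs end the intervention. Nothing there ends follow-up.
- **Primary outcome measure:** the TNSS change is obtained by "comparing the baseline score in each group with that at 6 months after treatment".
- **Statistical methods:** "The data analyses will be conducted on an intention-to-treat population".
- **Missing data and sensitivity analysis:** the data for the main analysis "should be collected in the fourth week of the treatment and at the half-year follow-up". Where they are missing, "we will use the multiple imputation adjustment approach", followed by sensitivity analyses.
- **Sample size calculation:** 39 per group is raised to 49 "to allow for a predicted 20-% dropout rate".

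No section provides for a month-6 assessment of someone who has been excluded.

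**The concern.** An intention-to-treat comparison needs the outcome of every randomized participant, whatever treatment was actually taken. The exclusion rule removes exactly those whose treatment did not go to plan, and it does so before the primary endpoint. It governs conduct, so the scores are never obtained and every later analysis must do without them.

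The loss is unlikely to be random. People may stop or deviate because their symptoms are poor or the treatment is troublesome. Patients and operators know the assignment, and 12 needling sessions differ greatly from a daily tablet, so exclusions could differ between arms in number and in kind. If warm needling loses more of the patients who later worsen, inferiority can be hidden. If loratadine loses more of them, warm needling is understated. The margin is only 0.2 TNSS points, so a small distortion matters.

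**Working it through.** **Inputs from the protocol.** Mean TNSS change 4.90 (SD 3.54) after acupuncture and 3.4 (SD 1.0) after loratadine; margin 0.2; power 80%; alpha 0.05, sidedness not stated; 39 per group, raised to 49 for 20% dropout.

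**Reproducing the plan's figures.**

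- Pooled SD = √((3.54² + 1.0²)/2) = 2.60. Planned difference = 4.90 − 3.4 = 1.5.
- With one-sided 0.025 and distance to the margin 1.5 + 0.2 = 1.7, 80% power needs 37 per group (normal formula) or 38 (t-based). The stated 39 is close. One-sided 0.05 gives 29 by the normal formula, so 0.025 is used below.
- 39/(1 − 0.20) = 48.75, so 49 per group, as stated.
- Power by non-central t at 1.5: 81.3% with 39 per group, 89.3% with 49.
- 20% of 49 is 9.8, so about 10 per arm could lack the month-6 score. The planned sample size is therefore not at fault.

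**Bias after imputation.** Let p_W and p_L be the exclusion rates in the warm-needling and loratadine arms. Let d be the number of points by which excluded patients do worse at month 6 than their earlier scores predict, with the same d in both arms. Imputation overstates each arm's mean improvement by p × d, so

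bias in (warm needling − loratadine) = (p_W − p_L) × d.

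With p_W = 0.20, p_L = 0.10 and d = 2, the bias is 0.10 × 2 = 0.20, equal to the margin.

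**Simulation.** All of the following are assumptions, apart from figures derived above: 49 per arm, SD 2.60 in each arm before any shortfall, one-sided 0.025, one earlier score correlated 0.7 with month 6, exclusion more likely when that score is poor (latent correlation 0.5), 12 imputations within arm by regression on that score, Rubin's rules, 14,000 runs. The true difference is −0.2, so declaring non-inferiority is an error.

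| Exclusion, warm needling v loratadine | d | Formula: −0.2 + bias | Mean estimate | False non-inferiority |
|---|---|---|---|---|
| 20% v 10% | 2 | 0.00 | 0.003 | 5.3% |
| 20% v 10% | 1 | −0.10 | −0.101 | 3.4% |
| 20% v 20% | 2 | −0.20 | −0.200 | 2.4% |
| 10% v 20% | 2 | −0.40 | −0.393 | 1.1% |

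Full follow-up in the same runs gives 2.5% to 2.6%. As a cross-check on the first row, an estimate centred 0.2 above the margin with SD 2.60 passes a one-sided 0.025 test with probability 5.7% at 49 per arm and 5.2% at 39. The simulated 5.3% lies between them.

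**Precision and power at a true difference of +1.5.**

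- 20% v 20%, d = 0: power 83.2% (78.9% if the correlation is 0.4), against 89% with everyone followed.
- 10% v 20%, d = 2: estimate 1.305, power 75.5%, against 83.6% with full follow-up. The full-follow-up figure is below 89% because the shortfall itself widens the spread of month-6 scores.
- 5% v 5%, d = 0, as if only consent withdrawals were lost: 88.5%.

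**The case against.** The strongest reply has four parts.

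1. **Non-collection is inferred.** The sentence is garbled, the Discontinuation section ends only the intervention, and the intention-to-treat statement suggests that everyone stays in the analysis. This is fair as to wording. But exclusion from the study plainly means no further visits, and the kindest reading of the trailing words keeps only the last score before exclusion, which is not month 6.
2. **Missing data are already provided for.** Reasons are recorded, the mechanism is examined, multiple imputation and sensitivity analyses follow, and a separate analysis plan is announced. The sample size allows for 20% loss, and 83% power still exceeds the planned 80%. This stands for precision, so no shortfall in sample size is claimed. It does not answer the bias. With no scores after exclusion, a different later course can be explored only by assumption.
3. **The numbers are stacked assumptions.** With SD 2.60 and correlation 0.7 the residual SD is 2.60 × √(1 − 0.49) = 1.86, so d = 2 is about 1.1 residual SDs, a large shift. At d = 0.5 with 20% v 10% the estimate is −0.15 and false non-inferiority about 2.9%, close to nominal. This stands: the figures show what could happen, not what will.
4. **Some loss is unavoidable.** Those who withdraw consent cannot be followed under any wording, and the 20% is total predicted dropout, not exclusion under this rule. This also stands, and the share that the fix would recover is unknown.

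A further argument is that retained deviators can dilute a difference, which is a particular worry in non-inferiority. A per-protocol set can still be formed from the recorded deviations. The reverse is impossible: uncollected scores cannot be added later.

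**Conclusion.** The concern holds. As written, the exclusion rule contradicts the intention-to-treat population and removes the primary endpoint for anyone who stops or deviates. Neither imputation nor a later analysis plan can supply the missing course.

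Direction and size are unknown, because the protocol gives no exclusion rates by arm. Under the assumptions above, bias ranges from none (equal exclusion, equal later course) to the whole margin of 0.2 in either direction (a 10-point difference in exclusion with d = 2). False non-inferiority then runs from 1.1% to 5.3%, against about 2.5% with full follow-up. Use of intranasal steroids within the permitted exception for severe symptoms is not a deviation, and comparing the arms regardless of it is not the error. The sentence should be changed; doing so is a cheap improvement.

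**What to change.** Replace the exclusion sentence in the Follow-up section with a rule to this effect: participants who discontinue or deviate from the intervention, or who use other medication, remain in the study; reasons and medication are recorded; TNSS is collected at every scheduled visit to month 6; follow-up ends only on withdrawal of consent; all randomized participants are analysed in their assigned arm. A per-protocol analysis can be kept as support, using the recorded deviations.

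The cost is slightly more follow-up, through the monthly contacts and the month-3 and month-6 assessments already planned. Sample size and primary test stay as they are.

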#### Concomitant care and intervention

During the treatment and follow-up period, the subjects are advised to avoid antigens. The participants are prohibited from taking medications such as oral and intranasal antihistamines, intranasal steroids, intranasal decongestant, antibiotics or oral leukotriene receptor antagonists. Only for patients with severe symptoms are intranasal steroids allowed to be used. The type of medicine, dosage and usage will be recorded in the diary card for analysis. For the other complicated chronic diseases, the patients must continue taking their routine medication and other therapies. The research staff will record the names of those diseases and the names of medications and therapies in the case report.

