#### Discontinuation of the intervention

The intervention is to be terminated in the cases of severe adverse events, withdrawal of participants by their own wish and unpermitted medication use.

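### The Follow-up section removes participants who stop or deviate from treatment from the study, so their month-6 primary outcome is not collected even where it could be

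*Protocol article*

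**What the plan says.** The rule is in the protocol article, Follow-up. Its trigger is broad: "In the event of participants discontinuing or deviating from intervention protocols". Its consequence is that "the study staff will record the reasons for this and their medications and then exclude the participants from the study". The sentence then ends with a clause on the latest outcome data that has no verb, so it is unclear whether those data are kept or dropped.

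Discontinuation of the intervention gives three grounds for ending treatment: "The intervention is to be terminated in the cases of severe adverse events, withdrawal of participants by their own wish and unpermitted medication use". Concomitant care and intervention lists the drugs that are not allowed during treatment and follow-up: "The participants are prohibited from taking medications such as oral and intranasal antihistamines, intranasal steroids, intranasal decongestant, antibiotics or oral leukotriene receptor antagonists". The next sentence makes an exception for intranasal steroids when symptoms are severe, with type, dose and usage entered on the diary card for analysis.

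The primary outcome is the change in TNSS, obtained by "comparing the baseline score in each group with that at 6 months after treatment during the follow-up period". Statistical methods states: "The data analyses will be conducted on an intention-to-treat population". Missing data and sensitivity analysis gives the aim, "In order to avoid missing data, we will provide an economic compensation for participants who have finished the trial and provided the completed data", and the remedy for what is still missing: "For these missing data, we will use the multiple imputation adjustment approach".

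**The concern.** Ending a treatment and ending a patient's participation are different decisions, and the Follow-up section merges them. A patient whose warm needling or loratadine is stopped in week 2 after a severe adverse event, or after taking an antihistamine, may be perfectly willing to be telephoned and scored at month 6. Under the rule as written, staff take that patient out of the study first.

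The missing values are then produced by the protocol rather than by the patient. They are also concentrated in people selected by what happened after randomisation. Patients and practitioners know the allocation, and the two treatments ask very different things of the patient (12 needling sessions against a daily tablet), so reasons for stopping or deviating may differ between the groups. An intention-to-treat analysis is meant to protect the comparison from this kind of selection. It does so less well when the month-6 values of the selected patients are imputed under an assumption that the collected data cannot test.

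**Working it through.** **1. Following one patient through the text.**
- Treatment is ended on one of the three grounds in Discontinuation of the intervention, or the patient deviates in some other way.
- Follow-up: reasons and medications are recorded and the patient is excluded from the study.
- No section schedules an assessment after exclusion.
- Primary outcome measure: the value needed is TNSS at 6 months after treatment.

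If the verbless clause means that the latest data are kept, those data stop at exclusion and do not include month 6. If it means that they are dropped, more is lost. Month 6 is missing on either reading.

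**2. Who is affected.**
- Severe adverse event or unpermitted drug: treatment ends, but the patient may still be reachable.
- Withdrawal by own wish: some will also refuse assessment and cannot be retained; others may only be refusing treatment.
- Intranasal steroid for severe symptoms: permitted, so this use alone need not lead to exclusion.
- Listed drug taken in months 1 to 6: treatment is already over, but the ban continues, so staff could read it as a deviation. The text does not settle this.

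**3. The plan's sample size.** Inputs from Sample size calculation: mean changes 4.90 (SD 3.54) and 3.4 (SD 1.0), power 80%, alpha 0.05, delta 0.2, 20% dropout. I read delta as TNSS points (assumption; the unit is not given).
- Sum of variances: 3.54² + 1.0² = 13.53; common SD = √(13.53/2) = 2.601.
- Distance to the margin: (4.90 - 3.4) + 0.2 = 1.7.
- n per group = 13.53 × (1.960 + 0.842)² / 1.7² = 36.75, so 37; a t-based calculation gives 38. This is one-sided 0.025 and close to the stated 39. One-sided 0.05 gives 29 or 30.
- Inflation: 39 / (1 - 0.20) = 48.75, so 49. Allowance: 49 - 39 = 10 per group.

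**4. What measured outcomes are worth in power.** Power is the probability that a noncentral t with 2n - 2 degrees of freedom and noncentrality 1.7 / (2.601 × √(2/n)) exceeds the one-sided 0.025 critical value.

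| Measured per group | Share lost | Noncentrality | Power |
|---|---|---|---|
| 49 | 0% | 3.24 | 89.3% |
| 44 | 10% | 3.07 | 85.8% |
| 39 | 20% | 2.89 | 81.3% |

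Up to 10 losses per group, from whatever cause, power stays above the planned 80%.

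**5. What selection could do (illustration with assumed values only).** Suppose a share f of one group is excluded and their true month-6 change is g points worse than the values that stand in for them. That group's mean is then overstated by f × g. For f = 5% to 20% and g = 1 to 3 points, the range is 0.05 × 1 = 0.05 to 0.20 × 3 = 0.6. With f = 10% and g = 2 the shift is 0.2, equal to delta if delta is in TNSS points. A shift in the warm needling group would favour non-inferiority, one in the loratadine group would work against it, and equal shifts would cancel. The documents give neither f nor g.

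**The case against.** **The intention-to-treat population is not contradicted.** A reader might infer that excluded patients leave the analysis set. The documents do not say so. The protocol plans to record the time and reason for missing data, consider the mechanism, impute, and run sensitivity analyses, and patients taken out of the study can remain in the analysed population through imputation. This stands, and no formal contradiction is claimed. What remains is that imputation would replace values that could have been collected.

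**Rescue use is partly protected.** A reader might infer that any listed drug ends follow-up. The exception for intranasal steroids shows otherwise, and its diary-card recording for analysis suggests that these users stay in. This stands and narrows the group. The other listed drugs, severe adverse events and other deviations are still caught. Whether a drug given for an adverse event or acute illness counts as unpermitted is not stated, and none of this depends on it.

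**The sentence is defective and the article condenses a fuller protocol.** True, and it limits certainty about the intent. But the exclusion clause itself is clear, and it is a stated instruction, not a detail left out.

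**The 20% allowance covers the loss.** For precision, it does. A reader might infer that the trial becomes underpowered, but that needs exclusions on top of the full allowance, and the documents give no reason to assume this. An assumed 5 extra per group would leave 34 and power of 75.7%; such exclusions can just as well be part of the predicted dropout. The allowance does not deal with selection.

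**Conclusion.** The point holds in this form: the Follow-up section does not separate stopping or deviating from the intervention from leaving the study, so the month-6 TNSS goes uncollected in patients who could still be assessed. This works against the aim of avoiding missing data and weakens the intention-to-treat analysis without formally contradicting it.

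The conclusion rests on the plain meaning of exclusion from the study and on the absence of any provision for later assessment. The number of patients is not given. Losses of up to 10 per group leave the planned 39. The range of shifts in the working shows only that a modest selective loss could be comparable to delta; it does not estimate a bias, and neither size nor direction can be taken from the documents. This should be changed, but it does not invalidate the design.

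**What to change.** Amend the Follow-up section so that participants who stop or deviate from the intervention, including after unpermitted medication, remain in outcome and safety follow-up to month 6 unless they withdraw consent to follow-up. Record the drug, dates and reason for use on the existing diary card. Analyse these participants in their randomised group, and exclude deviators only in a per-protocol or sensitivity analysis. Repair the unfinished clause at the same time, so that data collected before any withdrawal are clearly kept. Whether treatment itself continues after such a drug remains the sponsor's decision.

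The cost is about one sentence, one diary field and one supporting analysis. Monthly telephone and SMS contact and the daily diary of symptoms and other medication are already planned, and the sample size does not change. There is a small downside: some TNSS values will be recorded off treatment or under other medication, which may pull the groups together and so favour a non-inferiority conclusion. The per-protocol or sensitivity analysis is there to address this.

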### Intervention

#### Treatment group

Licensed acupuncture physicians will provide warm needling treatment three times a week for 4 weeks. The acupuncture needles are disposable and sterile and measure 0.25 × 25 mm and 0.25 × 40 mm (Suzhou Medicine Equipment Co., Ltd., Suzhou, China.). The moxa stick (Nanyang Lvying Moxibustion Product Co., Ltd., Nanyang, China) will be pure moxa measuring 12 mm in diameter and 15 mm in length. The acupuncture points used will be *Dazhui* (GV14), *Yintang* (EX-HN3), *Sibai* (ST2), *Yingxiang* (LI20), *Shangyingxiang* (EX-HN8), *Shangxing* (GV23), *Lieque* (LU7), *Chize* (LU5), and *Hegu* (LI4), which will be located according to the World Health Organization (WHO) International Standard Acupuncture Points. Patients will be in the seated position during treatment sessions. After routine skin sterilization, needles will be inserted using a neutral reinforcing and reduced manipulation technique. Each needle will be rotated until the arrival of *qi*. After the needle is obliquely inserted at *Dazhui* (GV14), the moxa stick will be ignited and attached to the needle handle with the ignited end toward the skin 1–1.5 cm from the skin surface. When the first moxa stick has burnt out, the ashes will be removed and the second stick will be replaced following the same procedure. In total, two moxa sticks are used. All needles will be retained for 30 min. Patients will feel a sense of local warmth, and the surrounding skin will become mildly red during the procedure. All of the practitioners have had more than 1 year of clinical acupuncture experience since completing a 5-year-long college of TCM training. The procedure for conducting warm needling therapy has been standardized in each center by training in advance (see Table 2).

**Table 2 Tab2:** Acupoints and needling procedure

Acupoints	Angle and direction	Depth (mm)
*Dazhui* (GV14)	Oblique insert downwards, then penetrate towards the acupuncture point *Shenzhu* (GV12)	26–32
*Yintang* (EX-HN3)	Transversely, downward	13
*Sibai* (ST2)	Transversely, towards the nose	8
*Yingxiang* (LI20)	Transversely, towards the root of nose	5
*Shangyingxiang* (EX-HN8)	Transversely, towards the nose	8
*Shangxing* (GV23)	Transversely, downward	8
*Lieque* (LU7)	Transversely, upward	8
*Chize* (LU5)	Perpendicular, upward	13–21
*Hegu* (LI4)	Perpendicular to the skin	21–26

Precautions: in the process of inserting the ignited moxa stick into the needle handle, acupuncture physicians hold the junction of the needle handle and needle body with one hand while inserting the moxa stick into the needle at *Dazhui* (GV14) gently with the other hand so as to prevent skin burns. After attaching the moxa stick to the needle handle, acupuncture physicians ensure the stick is fully fixed on the needle handle to prevent it from falling on to the skin surface. The patient will be closely monitored during the entire procedure by research assistants to ensure safety and that any accident is handled in a timely manner.

